### Interventions

#### Moodbuster Lite

Moodbuster Lite is a 4-week therapeutic course aimed at improving mood. It is a light-weight version of the Moodbuster for Depression intervention [26, 27] and consists of a web-based and a mobile component. Compared to Moodbuster for Depression, which also contains a number of cognitive therapy-based modules, the focus of Moodbuster Lite is on behavioral activation [28]. Through activity scheduling, participants learn to turn a “negative spiral,” with few pleasant activities leading to few positive stimuli, a low mood, and little incentive to perform more activities, into a “positive spiral,” with more pleasant activities leading to more positive stimuli, a better mood, and incentive to remain active. A secure web-based platform provides access to online lessons, homework exercises, a mood graph, and a calendar. A smartphone application, designed for both Android and iOS, prompts participants three times a day with a request to rate their current mood, and an overview of the participant’s responses is shown in both the app and the web platform’s mood graph. The course consists of three lessons that were adapted from the Moodbuster for Depression intervention to fit the low-mood context of this study: (1) Introduction, (2) Psychoeducation, and (3) Pleasant activities. The first lesson has also been extended with some exercises based on motivational interviewing [29] to increase participants’ motivation for completing the course. For the purpose of the current study, an optional virtual coach has been embedded into the platform to provide automated support at the beginning and the end of every lesson and halfway through lesson 3, the longest lesson. For this study, participants are advised, but not obliged, to complete the intervention in a time span of 4 weeks. On completion, participants retain their access to the platform for about another 5 months. An overview of the intervention is shown in Table 2.

**Table 2 Tab2:** Overview of the Moodbuster Lite course as used in this pilot RCT

	Lesson 1	Lesson 2	Lesson 3
**Topic**	Introduction	Psychoeducation	Pleasant activities
**Time frame**	Week 1	Week 1	Weeks 2–4
**Length**	22 pages	11 pages	17 pages
**Conversations with virtual coach**	2	1–2	2–3

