##### Conversations

The conversations have been designed in collaboration with a licensed therapist and are based on guidelines for e-coaching [35] and principles of motivational interviewing [29]. Some examples of guidelines for providing feedback we have applied are to (1) use correct greetings and closings; (2) use communication skills such as beginning a message with a compliment; (3) structure feedback, for example by not giving feedback on more than two subjects; (4) refer to things the participants have done, such as completing exercises or recording their moods; and (5) keep text readable by using short, clear sentences. With regard to the motivational interviewing, we have focused on increasing an individual’s willingness to change behavior, as well as on their confidence in their ability to do so, both of which are important for being “ready” to change. Baseline values of a participant’s willingness to change and confidence in their ability to do so are established using the *importance and confidence ruler* exercises in lesson 1 of the intervention. If importance or confidence is low, the virtual coach presents specific exercises aimed either at increasing the discrepancy between a participant’s goals and their current behavior and emphasizing the importance of change, or at enhancing a participant’s self-efficacy and emphasizing confidence in their ability to change. These elements have been incorporated into all the conversations except the introductory and final ones, thus providing us with the general conversation structure shown in Table 3. Conversations after each lesson always take place, focused on providing feedback, while conversations before a lesson take place only if motivation is considered low or if the previous lesson received a negative evaluation. Such evaluations can be given by free text input at the end of each lesson, and a sentiment analysis algorithm [36] is used to determine its valence (negative or positive).

**Table 3 Tab3:** The differential stages in the conversations

Stage	Before the lesson	After the lesson
1	Greeting	Greeting
2	Compliment or positive note	Compliment or positive note
3	Reflection on evaluation of previous lesson	Reflection on current lesson
4	Re-evaluation of confidence or willingness	Confidence or importance work
5	Reference to current lesson	Reference to next lesson
6	Goodbye	Goodbye

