### Primary outcome measures

#### Adherence

The primary outcome measure will be intervention adherence. According to the definition we have adopted, “adherence” describes the extent to which individuals are exposed to the content of the intervention [37]. Previously, this has been operationalized by dividing the number of completed sessions or modules by the maximum number [38], but because our 3-lesson course is relatively short, we will use the completed and maximum numbers of pages that make up the lessons. Including conversations with the coach, lesson 1 has 22 pages (20 in the control condition), lesson 2 has 13 (11 in the control condition), and lesson 3 has 20 pages (17 in the control condition). As a secondary way of measuring adherence, we will look at the *ecological momentary assessment* of mood via the smartphone application, whereby (similarly to adherence to the intervention content) we will operationalize adherence as the number of mood assessments made divided by the maximum possible number. There will be three mood assessments every day, meaning that participants can answer a maximum of 84 mood rating requests during the 4 weeks of the study.

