### Statistical analysis

#### Primary analysis

The primary analysis will focus on the preliminary effectiveness of the virtual agent with respect to intervention adherence, as assessed in terms of intervention completion and mood recording response rates. Intervention completion will be assessed by calculating point estimates with corresponding 95% confidence intervals for both the intervention and the control group; a general linear model will be used to estimate the preliminary effect at the alpha < 0.05 significance level. That information will enable us to calculate the sample size required for observing a similar intervention effect in a larger RCT. To assess the mood recording response rate, we will conduct a logistic mixed-effects analysis to determine variations in adherence over time, following a similar analysis we performed in a previous ecological momentary assessment study [52].

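### Table 2 and the adherence definition disagree by two pages on the length of lesson 1, which feeds the denominator of the primary outcome

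*Protocol article*

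**What the plan says.** The Adherence section, under the primary outcome measures, sets the ratio: "we will use the completed and maximum numbers of pages that make up the lessons". It then gives the maxima by arm, with coach conversations counted as pages in the intervention arm. The first of them reads "lesson 1 has 22 pages (20 in the control condition". The intervention and control figures are 13 and 11 for the second lesson, and 20 and 17 for the third.

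Table 2, in the Moodbuster Lite section, gives one set of lengths for the three lessons, "22 pages 11 pages 17 pages", with no split by arm. A separate row gives the number of coach conversations as 2, 1–2 and 2–3.

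The ranges in that row follow from the Conversations section, which says that "conversations before a lesson take place only if motivation is considered low or if the previous lesson received a negative evaluation". Conversations after a lesson always occur.

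The Primary analysis section takes intervention completion into a model: "a general linear model will be used to estimate the preliminary effect at the alpha < 0.05 significance level". The result is to inform the sample size of a larger trial.

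**The concern.** Table 2 agrees with the control-arm counts for lessons 2 and 3 and with the intervention-arm count for lesson 1, so its page row mixes two bases. Its total matches neither arm. Read as content pages, as the separate conversation row suggests, it puts lesson 1 at 22 pages without the coach, where the Adherence section puts it at 20.

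The page count is the denominator of the primary outcome. If the Adherence section held the wrong figure, every completion score would be off and a participant who finished the course could score above 100%. The outcome also feeds the means and standard deviations meant for planning the next trial.

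The same comparison brings out a second feature of the denominator. The intervention maximum counts every possible coach conversation, although some are offered only under certain conditions.

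**Working it through.** **Inputs**

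| | Lesson 1 | Lesson 2 | Lesson 3 | Total |
|---|---|---|---|---|
| Adherence section, control | 20 | 11 | 17 | 48 |
| Adherence section, intervention | 22 | 13 | 20 | 55 |
| Table 2, pages | 22 | 11 | 17 | 50 |
| Table 2, conversations (min–max) | 2–2 | 1–2 | 2–3 | 5–7 |

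**Step 1: reproduce the intervention maxima.** Assume one page per conversation. This is an inference, but the arm differences support it: 22 − 20 = 2, 13 − 11 = 2 and 20 − 17 = 3, which equal Table 2's maximum conversations lesson by lesson.

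- From the Adherence section's control counts: 20 + 2 = 22, 11 + 2 = 13, 17 + 3 = 20, total 55. This matches the stated intervention counts exactly.
- From Table 2's own page row: 22 + 2 = 24, 11 + 2 = 13, 17 + 3 = 20, total 57. This fails in lesson 1, by 2 pages.

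**Step 2: locate the conflict.** Table 2 minus control is +2, 0, 0. Table 2 minus intervention is 0, −2, −3. The differences of 2 and 3 in lessons 2 and 3 are coach pages that Table 2 lists in its other row, so they are no contradiction. What remains is 2 pages in lesson 1. With 20 in that cell, Table 2 would total 20 + 11 + 17 = 48 and the two places would agree.

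**Step 3: scores if the Adherence section is right.**

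- Control completer: 48/48 = 100%.
- Intervention completer with all 7 conversations: (48 + 7)/55 = 55/55 = 100%.
- Intervention completer with the minimum of 5: (48 + 5)/55 = 53/55 = 96.4%.

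No score exceeds 100%. The shortfall of up to 100 − 96.4 = 3.6 points occurs in the intervention arm only. It falls on those for whom the pre-lesson conversations are not triggered, that is, those with adequate motivation and no negative evaluation of the previous lesson.

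**Step 4: scores if Table 2's 22 is the true content count and the stated maxima are kept.** True totals would be 50 (control) and 50 + 5 = 55 to 50 + 7 = 57 (intervention).

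- Control completer: 50/48 = 104.2%.
- Intervention completer: 55/55 = 100% to 57/55 = 103.6%.
- Shift in control: 2/48 = 4.17 points. Shift in intervention: 2/55 = 3.64 points. Change in the between-arm gap: 4.17 − 3.64 = about 0.5 points.

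**The case against.** The strongest reply is that the section defining the outcome already fixes the denominator. It states a maximum for each arm, 55 and 48, and these are consistent with the conversation counts. Table 2 is a descriptive overview, and neither the Adherence section nor the Primary analysis section refers to it. A slip in one cell of such a table changes no score. This stands, and it limits the point to a contradiction to be reconciled.

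A reader might go further and infer three things that the article does not support:

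- **That the denominator is not fixed.** It is stated for each arm. It is contradicted elsewhere by two pages, which is less.
- **That scores above 100% are built into the outcome.** They arise only if the Adherence section is the wrong one, or if an analyst used Table 2's total of 50. With 50 for both arms, a control completer would score 48/50 = 96% and an intervention completer 53/50 to 55/50 = 106% to 110%, but nothing in the article calls for that total.
- **That the error creates a sizeable spurious difference between arms.** A miscount common to both arms moves the gap by about 0.5 points. A miscount in control alone would mean that lesson 1's two conversations add no pages, against the pattern in lessons 2 and 3 and against the statement that the intervention counts include conversations.

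It can also be objected that a common denominator changes an outcome deliberately defined with arm-specific maxima, and that a misprint alone does not justify this. That is fair. The case for the change rests on the conditional conversations, and whether the maximum is reduced when one is not offered may be settled in an analysis plan that is not shown. Taken literally, though, a stated maximum of 55 is not reduced.

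**Conclusion.** The point holds in a limited form. The two places give lesson 1 different content lengths, 22 and 20 pages, and Table 2's total of 50 fits neither arm. The likeliest explanation is a slip in Table 2's lesson 1 cell, which should then read 20. This rests on the inferred one page per conversation, which fits all three lessons. The article alone cannot prove it; the platform can.

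If the slip is in Table 2, no adherence score changes. If it is in the Adherence section, completers score up to about 104% in either arm, with little effect on the comparison between arms.

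The larger effect on the comparison comes from the fixed 55: up to 3.6 points against intervention completers who are not offered the conditional conversations, assuming that the maximum is not adjusted for them. Severity is minor to moderate. It is a correction to make before scoring and does not threaten the trial.

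**What to change.** 1. Count the lesson 1 pages on the platform in both conditions and correct whichever of Table 2 or the Adherence section is wrong.
2. Show content pages and coach pages in separate rows for each lesson. If the Adherence section is right, these are 20, 11 and 17 content pages (48) and up to 2, 2 and 3 coach pages (7).
3. Score the primary outcome in both arms as content pages completed over the common content total (48 if the Adherence section is right), and report coach pages separately in the intervention arm. Decide this before the log data are exported.

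The cost is a page count, one corrected cell or sentence, and a short change to the outcome definition, to be recorded as a protocol change. The log data must distinguish coach pages from content pages. The downside is small: exposure to coach pages no longer counts in the primary score. In return, completers score 100% in either arm and the arms are compared on the same material.

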### Secondary outcome measures

#### Motivation

Motivation for taking part in the intervention will be assessed in both groups by the Short Motivation Feedback List (SMFL) [39]. It consists of eight 10-point Likert-scale items ranging from “completely disagree” to “completely agree,” designed to capture the level and type (external, introjected, or identified) of a patient’s treatment motivation. The SMFL is based on self-determination theory [40] and has been found to have a congeneric reliability ranging from 0.81 to 0.93 [39]. There are two different versions. The pre-intervention version will be assessed at baseline (T_0_) and the post-intervention version after 4 weeks (T_1_). Motivation to continue using the intervention will be assessed by a single statement, “I intend to continue using the platform to schedule and perform activities,” assessed on a 5-point Likert scale ranging from “completely disagree” to “completely agree.”

#### Relationship with the coach

After study completion (T_1_), participants in the intervention group will assess their relationship with the virtual coach on the Bond scale of the Revised Short Version of the Working Alliance Inventory (WAI-SR) [41, 42]. The WAI-SR rates the quality of the therapeutic relationship with the virtual coach, and it has been adjusted to our context by replacing the name of the therapist with the word “coach.” The Bond scale consists of four 5-point Likert-scale items ranging from 1 (seldom) to 5 (always). The final raw score may range from 4 to 20, with higher scores indicating a better bond between participant and coach. The psychometric properties of the questionnaire are satisfactory [42].

#### Acceptance of the coach

Acceptance of the virtual coach will be assessed in the intervention group after 4 weeks (T_1_) using a set of six 7-point Likert-scale items. This scale has been previously used to measure attitudes toward a virtual discharge nurse [13] and has been adjusted to our context of iCBT. An overview of the items is provided in Table 4. Participants are asked to elaborate on their answers to each of these questions in an open text format.

**Table 4 Tab4:** Self-report measures of attitudes toward the virtual coach

Measure	Question	Likert-scale extremes
Satisfaction	How satisfied were you with the virtual coach?	Not at all–Very satisfied
Usability	How easy was it talking to the virtual coach?	Easy–Difficult
Continue	How much would you like to continue working with the virtual coach if the course continued?	Not at all–Very much
Relationship	How would you characterize your relationship with the virtual coach?	Complete stranger–Close friend
Preference	Would you rather have followed the course with or without the virtual coach?	Definitely prefer no coach–Definitely prefer virtual coach
Adherence	How likely is it that you will follow the virtual coach’s advice?	Not at all likely–Very likely

#### System usability

Usability of the platform will be assessed after week 4 (T_1_) by the System Usability Scale (SUS) [43]. The SUS is composed of ten 5-point Likert-scale items with response options ranging from 0 (strongly disagree) to 4 (strongly agree). Total scores are converted to a scale ranging from 0 to 100, where higher scores are indicative of higher platform usability. The SUS is considered a reliable instrument, and scores higher than 68 indicate “good” usability [44].

#### User satisfaction

User satisfaction with the web-based intervention will be assessed by the Client Satisfaction Questionnaire for internet-based interventions (CSQ-I) [45], an adaptation of the original CSQ [46]. The CSQ-I is composed of eight 4-point Likert-scale items with response options ranging from “does not apply to me” to “applies to me.” Total scores range from 8 to 32, with higher scores indicating greater client satisfaction. The CSQ-I has been found to be a reliable instrument [45].

#### Mental health status

Mental health status will be assessed using the Depression subscale of the Hospital Anxiety and Depression Scale (HADS-D) [47], consisting of seven items, each assessed on a 3-point scale. Total scores range from 0 to 21, and higher scores indicate more severe depression symptoms. An often used cutoff score for the HADS-D is 8 or higher, standing for “relevant symptoms of depression.” The HADS has been shown to be a reliable and valid instrument in various populations [48].

#### Mood

Participants’ mood will be assessed through ecological momentary assessments on a smartphone application that works on both Android and iOS systems. The application prompts participants three times a day to rate their mood on a scale of 1 to 7 (see Additional file 3).

#### Reasons for non-adherence

At the end of the study, at T_1_, participants will be asked online whether they completed the intervention and used it for the full duration of the study. If their response is negative, they will be asked to provide a rationale for not having completed the intervention or the study.

#### Level of engagement with the intervention

The third lesson is designed to stimulate users to schedule, perform, and evaluate pleasant activities. The number of these activities over time is assessed through log file analysis. Whether participants keep scheduling and recording activities for the duration of the study is an indicator of their engagement with the course, and of whether it has managed to make them more active.

#### Other measures

Screening for mental health issues will be performed before group allocation (T−1) using the Patient Health Questionnaire-9 (PHQ-9) [49], in order to deter people with more severe issues from taking part in the study. The PHQ-9 is composed of nine statements, each scored on a scale of 0 (not at all) to 3 (almost every day). Total scores range from 0 to 27, with higher scores indicating more severe depression, and scores over 14 moderate to severe depression (see the “Exclusion criteria” section above). The PHQ-9 is considered to have good psychometric properties [50].

### Sample size

Since this study is a first in its sort, we know of no literature that indicates what effect size could be expected. Following the recommendation of Teare and colleagues [51], we plan to recruit 70 participants to determine the group means and standard deviations required for an estimation of the effect and sample sizes in a future RCT.

### Statistical analysis

#### Primary analysis

The primary analysis will focus on the preliminary effectiveness of the virtual agent with respect to intervention adherence, as assessed in terms of intervention completion and mood recording response rates. Intervention completion will be assessed by calculating point estimates with corresponding 95% confidence intervals for both the intervention and the control group; a general linear model will be used to estimate the preliminary effect at the alpha < 0.05 significance level. That information will enable us to calculate the sample size required for observing a similar intervention effect in a larger RCT. To assess the mood recording response rate, we will conduct a logistic mixed-effects analysis to determine variations in adherence over time, following a similar analysis we performed in a previous ecological momentary assessment study [52].

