**Methods/design:**

The study will employ a pilot two-armed randomized controlled trial design. The primary outcomes of the trial will be (1) the effectiveness of iCBT, as supported by a virtual coach, in terms of improved intervention adherence in comparison with unguided iCBT, and (2) the feasibility of a future, larger-scale trial in terms of recruitment, acceptability, and sample size calculation. Secondary aims will be to assess the virtual coach’s effect on motivation, users’ perceptions of the virtual coach, and general feasibility of the intervention as supported by a virtual coach. We will recruit *N* = 70 participants from the general population who wish to learn how they can improve their mood by using Moodbuster Lite, a 4-week cognitive-behavioral therapy course. Candidates with symptoms of moderate to severe depression will be excluded from study participation. Included participants will be randomized in a 1:1 ratio to either (1) Moodbuster Lite with automated support delivered by a virtual coach or (2) Moodbuster Lite without automated support. Assessments will be taken at baseline and post-study 4 weeks later.

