### Randomization and blinding

Participants will be randomly assigned by an independent researcher to either Moodbuster Lite with automated support (intervention group) or Moodbuster Lite without automated support (control group). That will take place in a 1:1 ratio and on the basis of a computer-generated block randomization table with random block sizes [25]. Group allocation cannot be blinded to participants, because a description of the study’s research aim—improving intervention adherence with automated support by a virtual coach—must be provided in the information letter; whether or not automated feedback is provided will hence be obvious to participants. The principal investigator, who coordinates the study and conducts the data analysis, will not be blinded to the participants’ group allocation.

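### The future RCT is to be sized on the adherence effect observed in this pilot, which 35 per arm estimates too imprecisely to give a reliable sample size

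*Protocol article*

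**What the plan says.** The abstract of the protocol article lists, as part of its second primary outcome, "the feasibility of a future, larger-scale trial in terms of recruitment, acceptability, and sample size calculation". The Sample size section explains that "we know of no literature that indicates what effect size could be expected" and continues: "we plan to recruit 70 participants to determine the group means and standard deviations required for an estimation of the effect and sample sizes". Allocation is equal (Randomization and blinding: "That will take place in a 1:1 ratio"), which gives the 35 per arm stated under Study design.

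Under Primary analysis, completion is summarised by point estimates with 95% confidence intervals for each group, and "a general linear model will be used to estimate the preliminary effect at the alpha < 0.05 significance level". The next sentence gives the use to be made of this: "That information will enable us to calculate the sample size required for observing a similar intervention effect in a larger RCT".

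The article names no smallest worthwhile difference in adherence. It does not say that only the SD will be carried forward, and it plans no allowance for the uncertainty of the effect estimate when the future size is computed.

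**The concern.** A sample size needs two inputs: a nuisance parameter (the SD) and a target difference. A pilot of 70 estimates the first usefully and the second poorly. The required number varies with the inverse square of the target difference, so error in that estimate is strongly magnified. A chance overestimate leads to an underpowered trial. A chance underestimate leads to one that is needlessly large or looks infeasible, and an observed effect of zero or below gives no number at all.

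Sample size calculation is a stated primary aim, so one of the pilot's main products would be unreliable. The article also says that no literature indicates an effect to expect, so there is no outside figure against which to correct a chance estimate. This is not detail left to another document: the article states the rule, and an analysis plan that followed it would inherit the problem.

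**Working it through.** **Inputs.** From the article: 70 participants, 1:1, so 70/2 = 35 per arm; alpha 0.05. Assumed, because the article does not say: a two-sided test, 80% power for the future trial, approximately normal data, no dropout. The article gives no effect size or SD, so the work is in SD units (d) over a range of true values.

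**The plan's own figure.** The 70 rests on a cited pilot-size recommendation with no effect, power or precision target, so there is no formula to reproduce.

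**Precision of the difference.** Half-width = t(0.975; 68 df) × √(2/35) = 1.995 × 0.239 = 0.477 SD. With 30 or 25 analysed per arm it becomes 0.52 or 0.57.

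**Implied future size.** n per arm = 2(1.960 + 0.842)²/d² = 15.70/d². With noncentral-t intervals for the observed d:

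| Observed d | 95% CI | n per arm at estimate | at upper limit | at lower limit |
|---|---|---|---|---|
| 0.3 | -0.17 to 0.77 | 175 | 27 | none |
| 0.4 | -0.07 to 0.87 | 99 | 21 | none |
| 0.5 | 0.02 to 0.97 | 63 | 17 | over 30,000 |
| 0.8 | 0.31 to 1.28 | 25 | 10 | 164 |

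A t-based calculation adds about one per arm (22 in place of 21 at the upper limit for d = 0.4).

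**Chance of a size wrong by more than twofold.** Because n varies as 1/d², the size is under half the requirement when the observed d exceeds √2 × true d. It is over twice the requirement, or not computable, when the observed d is below true d/√2. By hand at true d = 0.3, with standard error 0.239: P(observed > 0.424) = P(Z > 0.52) ≈ 0.30 and P(observed < 0.212) = P(Z < -0.37) ≈ 0.36, a total of about 0.66. With the noncentral t distribution:

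| True d | too small | too large or not computable | total |
|---|---|---|---|
| 0.2 | 37% | 40% | 77% |
| 0.3 | 31% | 36% | 66% |
| 0.4 | 25% | 31% | 56% |
| 0.5 | 20% | 27% | 47% |
| 0.8 | 10% | 17% | 27% |

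**What the next trial would look like at true d = 0.3** (requirement 175 per arm; simulated). About 10% of pilots show a zero or negative effect and give no size. Among the rest, the 10th to 90th percentile of the computed size is about 40 to 1,750 per arm. True power of the resulting trial is below 80% in 56% of cases and below 50% in 33%.

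**Contrast with the SD.** The 95% limits of the pooled SD on 68 df are √(68/χ²) = √(68/92.69) to √(68/47.09), or 0.86 to 1.20 times its estimate. Squared, this changes N by a factor of 0.73 to 1.44. If the target were fixed at, say, d = 0.4 (an illustration only), 99 per arm would carry a range of about 73 to 143. A one-sided 80% upper limit for the SD multiplies N by 68/58.04 = 1.17.

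**The case against.** The strongest reply is that one sentence is being read as a binding algorithm. The article says the information will make a calculation possible. It labels the effect preliminary, reports confidence intervals, and collects SDs as well as means. A future trial would have its own sample size justification, and everything needed to size it differently will have been collected. Part of this stands. Nothing in the pilot's conduct or estimates is invalidated, and the choice can still be corrected when the next trial is designed. It does not remove the point: the stated target is an effect similar to the one observed, the Sample size section carries the effect forward together with the SDs, and the intervals promised for completion are described for each group, with no statement that they will temper the target.

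Three stronger readings are tempting but not supported.

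- A reader might infer that the larger trial goes ahead only after a significant pilot result. That would select inflated estimates, but no section states such a condition. The 0.05 level is attached to estimating the preliminary effect, and the Discussion says only that the estimate will help determine feasibility and necessity.
- A reader might infer that the next trial will probably be badly mis-sized whatever the truth. That depends on the unknown true effect: the chance is above one half for true d of 0.2 to 0.4, about even at 0.5 and about 27% at 0.8.
- A reader might infer that 70 is too few. For estimating an SD it is reasonable.

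**Conclusion.** The point holds as a criticism of how the effect estimate is to be used. A between-group difference known only to about ±0.48 SD cannot fix the size of a later trial: across true differences of 0.2 to 0.5 SD, roughly half to three quarters of pilots would give a number wrong by more than twofold, or none. These figures assume a two-sided 5% test, 80% power, full retention and a normal approximation to a bounded adherence proportion. Dropout would widen the interval, and 90% power gives the same pattern. The point should be fixed, but it is not a threat to the validity of this trial.

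**What to change.** Keep N = 70. Replace the sizing sentence under Primary analysis, and align the Sample size section, along these lines: the pilot will supply the SD of adherence, the control-group mean, and the recruitment and retention rates; the future RCT will be powered on a smallest worthwhile difference in adherence, fixed before the pilot data are seen. Stating that difference in adherence units lets the pilot SD do its work. A cautious choice is the one-sided 80% upper limit of the SD, which multiplies N by 1.17 (in the illustration above, 99 × 1.17 ≈ 116 per arm). Report the pilot between-group difference with its 95% confidence interval, as preliminary.

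Do not replace the sentence with a rule that progression depends on whether that interval contains the worthwhile difference. At this width such a rule barely discriminates: a target of d = 0.4 lies inside the interval in 62% of pilots when the true effect is zero.

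The cost is a change of wording and one figure that the team must agree in advance. Design, data collection and the planned model are unaffected.
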